Side effects checklist (adverse events)			✓	✓			
fMRI		✓				✓	
MRI		✓				✓	
rsfMRI		✓				✓	
MRS		✓				✓	
Diffusion-weighted imaging		✓				✓	

BDI-II, Beck Depression Inventory-II; CTQ, Childhood Trauma Questionnaire; EQ-5D-5L, EuroQoL-five-Dimensions-5-Level; GAD-7, Generalised Anxiety Disorder-7; HDRS-17, Hamilton Depression Rating Scale-17; MGH, Massachusetts General Hospital; MRS, MR spectroscopy; QIDS-SR, Quick Inventory of Depressive Symptomatology; rsfMRI, resting state functional MRI; SCID-5, Structured Clinical Interview-5; THINC-it, THINC-Integrated Tool; WSAS, Work and Social Adjustment Scale.

Secondary outcome measures are the Beck Depression Inventory-II,^29^ Patient Health Questionnaire,^30^ Generalised Anxiety Disorder Assessment,^31^ Work and Social Adjustment Scale,^32^ EuroQol-five-dimensions-5-level,^33^ and cognitive functioning as measured by the THINC-Integrated Tool (THINC-it) (THINC-it Task Force, http://thinc.progress.im/en). Quick Inventory of Depressive Symptomatology^34^ is completed for a mechanism study (see online supplementary material appendix 2).

In addition, a purposely designed patient proforma will be used to collect patient NHS service utilisation information at the 16 and 26 weeks follow-up time points. This will cover relevant items listed in the Client Service Receipt Inventory,^35^ and tailor the resources items measured following good practice approaches used by the health economics database of instruments for resource use measurement group to estimate costs. Patient acceptability will be measured on a 1–5 scale from unacceptable to acceptable and patient experience of overall improvement will be assessed using the Patient Global Impression of Change (1–5 scale much worse to much better)^36^ after each TMS session and at each follow-up time point. A side effect checklist will be completed after each TMS session and 8 weeks follow-up assessment. We will note any changes in medication or other forms of treatment.

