### Statistical analyses

#### Efficacy analysis

The primary analysis will test the null hypothesis that treatment with cgiTBS does not increase response rate as measured by HDRS-17 compared with rTMS at 16 weeks on an intent to treat population with any missing response data at 16 weeks being imputed as no response having been achieved. Response at 16 weeks was selected as the primary outcome because of the much larger response rate with cgiTBS than rTMS in our pilot study.^21^ A logistic regression will be fitted for the outcome of response with treatment arm, centre, baseline HDRS-17 score and MGH TRD score.

As a secondary analysis a logistic regression model will be repeated in completers (those with 10 or more rTMS or cgiTBS treatments, assessed at baseline and 16 weeks) and a per-protocol analysis. Secondary outcomes are the and proportion of responders and remitters at 8, 16 and 26 weeks, and sustained responders at both 16 and 26 weeks will be compared between groups using logistic regression adjusted for treatment centre, baseline HDRS-17 score and MGH TRD score (5% significance). All outcomes are shown in table 3. Repeated measure linear models will be used for continuous outcomes. Patient acceptability (5-point scale) and safety of both cgiTBS and rTMS (side-effects checklist) will be reported descriptively.

**Table 3 T3:** Study efficacy outcome measures

Outcomes	Measure	Time points
Primary Outcome	17-Item Hamilton Depression Rating Scale (HDRS-17)	Response at 16 weeks (defined as by a 50% or greater reduction in HDRS-17 score from baseline)
Secondary Outcomes	HDRS-17	Mean change in HDRS-17 score compared with baseline at 8, 16 and 26 weeks Response (as defined above) at 8 weeks and at 26 weeks Sustained response at 16 and 26 weeks (defined as a continuing response as defined above following a response at the previous time point) Remitters at 8, 16 and 26 weeks (defined as a score of 7 or less on the HDRS-17)
	Beck Depression Inventory-II	At 8, 16 and 26 weeks
	Patient Health Questionnaire Quick Inventory of Depressive Symptomatology	At 8, 16 and 26 weeks At 8, 16 and 26 weeks
	Generalised Anxiety Disorder Assessment	At 8, 16 and 26 weeks
	THINC Integrated Tool	At 8, 16 and 26 weeks
	EuroQol-five-Dimensions-five-Level	At 8, 16 and 26 weeks
	Work and Social Adjustment Scale	At 8, 16 and 26 weeks
	Patient Acceptability (1–5 scale)	After each TMS session and at 8, 16 and 26 weeks
	Adverse Events Checklist	After each TMS session and 8 weeks

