### Safety considerations

Internationally agreed definitions of adverse events (any untoward medical occurrence in a clinical trial subject administered TMS whether or not it has a causal relationship with TMS) and serious adverse events (any adverse event or adverse reaction that results in death, is life-threatening, requires hospitalisation or prolongation of existing hospitalisation, results in persistent or significant disability or incapacity, or is a congenital anomaly or birth defect). All participants will be asked about adverse events after every treatment (immediately and a maximum of 72 hours later) until they are resolved. Any participant found to be at risk to themselves (suicide, neglect) or others, or developing a serious adverse event will be referred to relevant clinical services. A review by a clinical expert in TRD will be offered to any participant whose depression has become more severe at 16 and 26 weeks for safety reasons.

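### The side-effects checklist ends at week 8 while efficacy is compared to week 26, so new non-serious events after week 8 have no scheduled enquiry in the article (minor, cheap to improve)

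*Protocol article*

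**What the plan says.** Three places in the protocol article give the same checklist schedule.

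- Study schedule, text: "A side effect checklist will be completed after each TMS session and 8 weeks follow-up assessment".
- Table 2: the checklist row, labelled as covering adverse events, is ticked for the treatment period and week 8 and is blank at weeks 16 and 26.
- Table 3: "After each TMS session and 8 weeks". The patient acceptability row directly above it reads "After each TMS session and at 8, 16 and 26 weeks".

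The Efficacy analysis section ties the safety report to this instrument: "safety of both cgiTBS and rTMS (side-effects checklist) will be reported descriptively". It also compares responders and remitters by arm at 8, 16 and 26 weeks, and sustained response at 16 and 26 weeks.

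The Safety considerations section adds an enquiry linked to treatment: "All participants will be asked about adverse events after every treatment (immediately and a maximum of 72 hours later) until they are resolved". For the later visits it gives a clinical review "offered to any participant whose depression has become more severe at 16 and 26 weeks for safety reasons". It also says that a participant found to be at risk or "developing a serious adverse event will be referred to relevant clinical services", with no week attached.

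**The concern.** The trial's rationale is durability: the Introduction suggests that iTBS may produce longer-term network change, and efficacy is followed to week 26. A reader weighing lasting benefit will want harms described over the same period. Participants already attend at weeks 16 and 26, yet the only instrument named for the safety report is not used there.

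The category affected is narrow: new, non-serious events that begin after week 8. Hypomania is one example. Table 1 excludes people with a bipolar history because of the risk of mania, and none of the scales scheduled at weeks 16 and 26 is described as a mania measure. A mild episode in month four could pass without any scheduled question.

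The primary outcome, the sample size and the error rates are not at stake.

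**Working it through.** The article states no figure for safety coverage, so the check compares schedules and then does simple arithmetic on the weeks.

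**Inputs**
- Treatment: 20 sessions over 4 to 6 weeks (Interventions). Randomisation immediately precedes the first session (Randomisation), so weeks since randomisation are weeks since treatment began.
- Follow-up visits: weeks 8, 16 and 26, each with a window of ±1 week (Table 2).
- Last checklist: week 8 (Study schedule, Tables 2 and 3).
- 184 participants per arm, with 15% lost by week 16 (Sample size).

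**Step 1: is exposure covered?** The last session falls at week 4 to 6. The week-8 checklist comes 8 − 6 = 2 to 8 − 4 = 4 weeks later, or 7 − 6 = 1 to 9 − 4 = 5 weeks with the window. All of the exposure period is covered, plus a short post-treatment interval.

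**Step 2: how long is the uncovered interval?** Nominally 26 − 8 = 18 weeks. With the windows it is 25 − 9 = 16 to 27 − 7 = 20 weeks. As a share of follow-up, 18/26 = 69%, and 2 of the 3 follow-up visits have no checklist. The 69% counts weeks of follow-up, not weeks of exposure, none of which is uncovered.

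**Step 3: does anything else at weeks 16 and 26 ask about new adverse events?**

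| Source | What it gives after week 8 | Asks about new adverse events? |
|---|---|---|
| Enquiry in Safety considerations | Starts from a treatment session and follows events to resolution | No, sessions end by week 6 |
| GAD-7, THINC-it, WSAS, EQ-5D-5L | Anxiety, cognition, function, quality of life | No, indirect |
| Service-use proforma | Healthcare contacts | No, indirect |
| Global impression of change | Overall improvement or worsening | No |
| Noted treatment changes ("We will note any changes in medication or other forms of treatment") | May reveal an event that led to treatment | No, indirect |
| Review of worsened depression | Clinical review of those who are worse | No, one condition only |

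**Step 4: illustrative size.** The article's sample size reproduces: the two-proportion formula with pooled variance, 26.5% against 41.5%, two-sided 5% and 80% power, gives 156 per arm, and 156/0.85 = 183.5, rounded up to 184. The article gives no risk of late non-serious events, so the risks below are assumptions. The 15% loss is stated for week 16; carrying it to week 26 is a further assumption, so the no-loss case is also shown.

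| Assumed 18-week risk | Per arm, 184 × 0.85 = 156 | Per arm, no loss (184) |
|---|---|---|
| 2% | 3.1 | 3.7 |
| 5% | 7.8 | 9.2 |
| 10% | 15.6 | 18.4 |

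These are counts of people whose event would have no scheduled enquiry. No difference between arms is assumed, and many such events would be unrelated to stimulation.

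**The case against.** The strongest reply is that the schedule is a defensible choice. The three places agree, so nothing is contradicted. For a short, non-drug exposure, enquiry after every session plus a check some weeks later covers the period in which stimulation effects are most likely. No specific late harm that differs between two active TMS arms has been shown. The week-16 and week-26 measures give structured by-arm information on domains where a lasting effect might appear. The article is also a condensed account: the full protocol may say how adverse events outside the checklist are recorded at later visits.

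Much of this stands. It narrows the loss, keeps the point minor and lowers confidence. Two things remain. The shorter schedule is stated outright, next to an acceptability row that runs to week 26, so it was not lost in condensing. And none of the indirect measures asks every participant about new events.

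A reader might go further and infer that safety oversight stops at week 8. The documents do not support that. No week-8 limit is set on serious adverse events, worsened depression triggers an offer of review at weeks 16 and 26, and Ethical considerations describes an independent data monitoring committee. Nor does the 69% mean that most of the relevant risk period is missed, since exposure ends by week 6.

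**Conclusion.** The point holds as a minor, low-cost improvement, with low to medium confidence. As the article sets it out, non-serious safety is described by arm to about week 8 and efficacy to week 26. What is lost is a by-arm description of new non-serious events over a nominal 18 weeks (16 to 20). Acute stimulation effects are probably captured, and the primary result does not change.

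This rests on the article alone. It assumes that the full protocol adds no adverse-event enquiry at weeks 16 and 26; if it does, the point falls away apart from the wording of the safety analysis. The patient counts rest on assumed risks and do not show that any comparison between arms would change.

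**What to change.** - In Tables 2 and 3, add a brief adverse-event enquiry covering the time since last contact at the week-16 and week-26 visits. Ask it after the HDRS-17 so that the answers cannot colour the primary rating.
- In the Efficacy analysis section, state that adverse and serious adverse events will be reported descriptively by arm to week 26.
- If the enquiry is not added, state that conclusions on non-serious safety apply to week 8 only.

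The cost is two ticks in Table 2, one line in Table 3, a sentence of analysis text and a few minutes at two visits that already take place. Some recorded events will be unrelated to stimulation. The sample size and the primary analysis are unchanged. With recruitment suspended in April 2020 and completion due in September 2021, the change could still cover visits not yet held.

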### Interventions

For all treatments, a 70 mm figure-of-eight coil (E-z Cool coil) and a Magstim Horizon Performance Stimulator with StimGuide Navigated TMS Package (Magstim Company, Whitland, UK) will be used. Participants in both treatment arms will receive neuronavigation-guided single coil stimulation for 20 TMS sessions delivered over 4–6 weeks. A total of 3000 pulses will be delivered in each rTMS or cgiTBS session. Each treatment session, irrespective of treatment arm, is designed to last approximately 37.5 min in total for the purposes of blinding the participants and assessors of outcome. There must not be a gap of more than 4 days between treatments in the course of 20. Medication will be unchanged over 16 weeks follow-up unless there is clinical risk of harm.

Individuals assigned to cgiTBS will receive bursts of three pulses (80% motor threshold) at 50 Hz applied at a frequency of 5 Hz (ie, every 200 ms) for 40 s duration over a site determined from the assessment of maximal strength of effective connectivity between the rAI and the left DLPFC from fMRI and structural MRI. Neuronavigation computes the nearest location for TBS stimulus on the scalp from an individualised head model based on structural MRI and three fiducial points, the nasion, left preauricular and right preauricular sites. If this site causes discomfort to the participant, it is moved by 1 cm in any direction until there is no discomfort. The pulses are repeated for a total of 5 runs with 5 min rest intervals between runs.

Individuals assigned to rTMS will follow the standard US Food and Drug Administration approved protocol. The site of stimulation will be determined using structural and fMRI utilising neuronavigation to compute the F3 electrode site over the left DLPFC for TMS stimulation from the same head model and three fiducial points. Stimulation is at 120% motor threshold with 75×4 s trains of 10 Hz interspersed by 26 s intertrain intervals.

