### Study schedule

Trained researchers under the supervision of clinically trained investigators will obtain informed consent and undertake all assessments. A prescreening questionnaire will be used to telephone screen interested participants first, with potentially eligible participants invited to attend a baseline assessment. Written informed consent will be obtained and study eligibility determined at the baseline assessment.

Information on sociodemographics, medical and psychiatric history including a detailed assessment of treatment resistance will be obtained from case files and primary care notes. Diagnosis will be assessed by the Structured Clinical Interview^24^ for the Diagnostic and Statistical Manual of Mental Disorders, Fifth Edition (DSM-5).^25^

Treatment resistance will be measured by the Massachusetts General Hospital (MGH) TRD staging score (adapted for new treatment options—see online supplementary material appendix 1 and table 1).^26^

Depression severity and the primary outcome measure will be assessed using the GRID version of HDRS-17.^27^ The HDRS-17 and secondary outcome measures will be assessed in eligible patients at baseline, 8, 16 and 26 weeks postrandomisation (table 2). The primary outcome measure is a binary variable of responder or non-responder at 16 weeks. Individuals observed to have a 50% drop or greater in HDRS-17 from baseline to 16 weeks are defined as responders. In contrast, individuals with <50% reduction or a null value are classified as non-responders. The Childhood Trauma Questionnaire^28^ will be assessed at baseline as a moderator of treatment response at 16 weeks.

**Table 2 T2:** Study schedule and assessments

Outcome measures	Baseline assessment (consent to the study)	Baseline MRI scan	Treatment Monday–Friday for 4–6 weeks	8 weeks follow-up assessment	16 weeks follow-up assessment	16 weeks MRI scan	26 weeks follow-up assessment
Visit window		Within 14 days of Baseline Assessment	+14 days of MRI Scan	±1 week from Randomisation	±1 week from Randomisation	Within 14 days of 16 week Follow-up Assessment	±1 week from randomisation
HDRS-17	✓		✓Only if baseline assessment exceeds 4 weeks	✓	✓		✓
MGH	✓		✓ Only if Baseline assessment exceeds 4 weeks				
BDI-II	✓			✓	✓		✓
PHQ-9	✓			✓	✓		✓
WSAS	✓			✓	✓		✓
GAD7	✓			✓	✓		✓
EQ-5D-5L	✓			✓	✓		✓
THINC-it	✓			✓	✓		✓
SCID-5	✓						
CTQ	✓						
QIDS-SR	✓			✓	✓		✓
Client Resource Questionnaire	✓				✓		✓
Patient Acceptability			✓	✓	✓		✓

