### Randomisation

Randomisation will take place immediately prior to the start of the first treatment session, with participants randomised to either rTMS or cgiTBS treatments. Randomisation will be conducted via a web-based randomisation system (Sealed Envelope, www.sealedevelope.com) by a named TMS nurse practitioner and healthcare assistant delivering TMS at each centre who will remain un-blinded. Participants will be randomly assigned in a 1:1 ratio into the rTMS and cgiTBS arms using blocks of varying size. Randomisation will be stratified by centre and minimised on severity of depression at baseline and degree of treatment resistance. Baseline depression will be measured by HDRS-17 score and classified as moderate (16-23) or severe (≥24).^37^ Treatment resistance will be measured by the MGH TRD staging score and, based on distributions of treatment resistance in the Antiglucocorticoid augmentation of anti-Depressants in Depression (ADD) study,^38^ degree of treatment resistance will be classified as low (2–3.5), medium (4-6) and high (≥6.5).

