	MRI scan (structural (T1), diffusion-weighted imaging (DWI) for structural connectivity, resting state fMRI for functional connectivity (FC) and effective FC (eFC), and GABA MRS of the DLPFC and insula	T1, DWI, FC, eFC at baseline (all centres) GABA at baseline and T1, DWI, FC, eFC, GABA at 16 weeks (all sites except London).

DLPFC, dorsolateral prefrontal cortex; fMRI, functional MRI; MRS, MR spectroscopy; TMS, transcranial magnetic stimulation.

We will explore moderators of depression response at 16 weeks, namely severity of depression by baseline HDRS-17 score, degree of treatment resistance, childhood trauma and age. The number of TMS sessions attended will be explored as a mediator of outcome in exploratory subgroup analyses of the depression response at 16 weeks.

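### Sessions attended is a post-randomisation variable, so the planned subgroup analyses of it cannot estimate mediation (minor, exploratory analysis)

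*Protocol article*

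**What the plan says.** The last paragraph of the Efficacy analysis section of the protocol article deals with two kinds of variable.

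- **Moderators of 16-week response:** "namely severity of depression by baseline HDRS-17 score, degree of treatment resistance, childhood trauma and age". All four are fixed before allocation.
- **Sessions:** the number of TMS sessions attended "will be explored as a mediator of outcome in exploratory subgroup analyses of the depression response at 16 weeks".

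Two other sections fix the timing. Under Randomisation: "Randomisation will take place immediately prior to the start of the first treatment session". Under Interventions: "Participants in both treatment arms will receive neuronavigation-guided single coil stimulation for 20 TMS sessions". The planned number is therefore the same in both arms, and any variation in the number attended arises after allocation.

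The article names no model, adjustment set or causal method for the sessions analysis, and gives no expected distribution of attendance.

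**The concern.** A subgroup analysis asks whether the treatment effect differs across levels of a characteristic that treatment cannot have changed. A mediation analysis asks how much of the treatment effect passes through something that treatment may have changed. The sentence on sessions names the second aim and the first tool.

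Attendance can depend on tolerability, early benefit and underlying prognosis, and each of these may also bear on response at 16 weeks. Two things follow from grouping patients by attendance:

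1. Within an attendance group the two arms need no longer be comparable, because patients may reach that group for different reasons in each arm.
2. Response compared across attendance groups mixes any effect of sessions with the prognosis of those who keep attending.

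At stake is how one exploratory result is read. An attendance gradient reported under the name of mediation would carry a causal meaning that the analysis cannot support. The article's abstract says that further publications will examine moderators and mediators, so such a result is meant to be reported.

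**Working it through.** **Step 1: timing.** Randomisation precedes session 1, so sessions attended is wholly post-randomisation. The four moderators are pre-randomisation. The method suits those four and does not suit the fifth variable. This step needs no arithmetic.

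**Step 2: can a gradient appear with no session effect?** The plan attaches no figure to this analysis, so there is none to reproduce. The only anchor is the pair of response rates in the Sample size section, 26.5% and 41.5%, with midpoint (26.5 + 41.5)/2 = 34%. Everything else below is assumed.

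Model, with latent prognosis u ~ N(0,1) and no effect of arm or sessions on response:

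- logit P(response) = −0.8 + u, which gives 34.0% overall in both arms.
- logit P(10 or more sessions) = 2.6 + λu in arm A and 1.6 + λu in arm B.
- λ is the assumed strength of the link between prognosis and attendance.

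With a(u) and r(u) for the two probabilities:

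- Response in attenders = E[a·r] / E[a]
- Response in others = E[(1 − a)·r] / E[1 − a]

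Results by numerical integration over u, in percent (differences in percentage points):

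| λ | Attend, A / B | Response in attenders, A / B | Response in others, A / B | Gap within arm, A / B | B − A among attenders |
|---|---|---|---|---|---|
| 1 | 90.29 / 79.30 | 35.49 / 37.15 | 20.02 / 21.85 | 15.47 / 15.31 | 1.67 |
| 0.5 | 92.39 / 82.09 | 34.65 / 35.55 | 25.93 / 26.83 | 8.72 / 8.72 | 0.90 |
| 0.25 | 92.91 / 82.91 | 34.31 / 34.76 | 29.76 / 30.20 | 4.55 / 4.56 | 0.46 |
| 0 | 93.09 / 83.20 | 33.99 / 33.99 | 33.99 / 33.99 | 0 / 0 | 0 |

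Check at λ = 1, arm A: 0.9029 × 35.49 + 0.0971 × 20.02 = 33.99, the overall rate.

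The true effect of sessions is zero in every row. The gap within arm runs from 0 to about 15 points and the between-arm artefact among attenders from 0 to about 1.7 points.

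**Step 3: how far this depends on the assumptions.** These ranges describe the scenarios above and are not bounds. In a variant where prognosis and attendance are correlated normal variables, the gap is about 12 to 14 points at correlation 0.3 and 18 to 23 at 0.5. If stopping is tied to prognosis in one arm only, the between-arm artefact among high attenders is about 4 to 6 points. With no shared cause, both are zero.

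**Step 4: a second route.** The Study schedule section defines the outcome so that "individuals with <50% reduction or a null value are classified as non-responders". If that rule carries into this analysis (an inference), patients who stop both sessions and follow-up count as low attenders and as non-responders. The gap this creates is p × (share missing in low attenders − share missing in high attenders). Take the plan's 15% loss, p = 34%, and an assumed fifth of patients as low attenders:

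- 30% against 11.25% missing (0.2 × 30 + 0.8 × 11.25 = 15): 0.34 × 18.75 = 6.4 points.
- 50% against 6.25% missing (0.2 × 50 + 0.8 × 6.25 = 15): 0.34 × 43.75 = 14.9 points.

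**The case against.** The strongest reply is that this is one sentence in a condensed article, the analysis is called exploratory, and the detail belongs in an analysis plan that is not shown. The word *subgroup* may be loose drafting, since the text does not say that patients will be split by sessions or that arms will be compared within attendance groups. This limits the severity but does not remove the point. The article states a method, and the method does not fit the aim. The exploratory label speaks to multiplicity and strength of evidence, not to confounding.

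Three stronger readings are tempting, and the documents do not support them.

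- **That the artefact rivals the trial's target effect.** The 15-point target in the Sample size section is a difference between arms. The gap of up to about 15 points in the main illustration is between attenders and others within an arm. These are different quantities, and the match rests on one chosen value of λ.
- **That the completer analysis should be replaced for the same reason.** It takes "completers (those with 10 or more rTMS or cgiTBS treatments, assessed at baseline and 16 weeks", which also selects on events after randomisation. But it is a conventional secondary supplement to a stated intention-to-treat primary analysis, and it repeats that analysis's logistic regression. Replacing it would be a trade-off, not the correction of an error.
- **That the result would drive course length or booster plans.** The Discussion ties boosters to cgiTBS proving clinically effective and cost-effective. It does not tie them to sessions attended.

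One further objection stands and shapes the fix. A mediation model adjusted only for baseline variables does not remove confounding by early benefit or tolerability, which arise during treatment.

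**Conclusion.** The concern holds as a mismatch between aim and method. Subgroup analyses by sessions attended condition on a post-randomisation variable and do not estimate mediation. This conclusion rests only on the order of randomisation and treatment, which the article states.

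The size is uncertain. The figures of 0 to about 15 points within arm and 0 to about 1.7 points between arms among attenders rest on assumed links between prognosis and attendance and an assumed difference in attendance between arms. They show that a gradient can appear without any effect of sessions, not that one will.

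Severity is minor. The primary intention-to-treat test and the sample size are unaffected.

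**What to change.** Keep subgroup analyses for the four baseline moderators only. For sessions attended, choose one of two courses.

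1. **Estimate mediation.** In all randomised patients, fit a model for sessions attended given arm, and a model for 16-week response given arm, sessions and their interaction. Adjust both for baseline HDRS-17, MGH score, centre, age and Childhood Trauma Questionnaire score. Report direct and indirect effects. Add a sensitivity analysis for unmeasured and post-randomisation confounding, naming early benefit and tolerability. Show the result also without counting missing response as non-response.
2. **Describe only.** Drop the word mediator, report attendance by arm and its association with response, and state that the association is not causal.

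Either course needs a few lines of text. The first also needs some programming but no new data: the listed covariates are already collected, and the Economic analysis section says that sessions will be recorded. Its price is wider intervals and reliance on stated assumptions that the data cannot test.
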